### Safety and adverse events

Given the severely ill ICU population who regularly undergo hemodialysis, we anticipate potential complications. These events will only be considered adverse events if they are potentially related to the study treatment, are unexpected to the attending physician, and are unrelated to the underlying critical illness that led to RRT.

Serious adverse events will be those that are life-threatening, result in death, lead to prolonged hospitalization, or cause severe and permanent disability. Serious adverse events will be adjudicated by independent physicians and reported to the DSMB and ethics committees. Details on adverse events are available in the notes.

Information on adverse events will be collected. As this involves a critically ill ICU population, various physiological alterations are expected, including laboratory abnormalities and vital sign changes, as well as those resulting from ongoing treatments. Therefore, expected abnormalities will not be considered adverse events unless there is suspicion or confirmation that the event is related to the study intervention.

Adverse events of special interest - those already known to be associated with methylene blue, regardless of severity - will also be recorded. These include hypertension (defined as systolic blood pressure above 180mmHg), chest pain, nausea, vomiting, gastric reflux (defined as reflux greater than 500mL within 6 hours after the start of dialysis), malignant hyperthermia (defined as the occurrence of hyperthermia associated with muscle rigidity, metabolic acidosis, hypercapnia, and/or rhabdomyolysis), hemolytic anemia (defined by the presence of anemia accompanied by clinical signs such as jaundice, together with laboratory evidence of red blood cell destruction such as elevated lactate dehydrogenase - LDH, increased indirect bilirubin, low haptoglobin, and/or reticulocytosis) and worsening of gas exchange, defined as a ≥ 20% decrease in the in partial pressure of oxygen in arterial blood/fraction of inspired oxygen (PaO_2_/FiO_2_) ratio as an absolute increase of 20% in FiO_2_ requirement, if blood gases were not available. In addition, any adverse events deemed by investigators to be possibly related to the study drug must also be documented. These data will be collected only within the first 24 hours following the drug infusion.

Serious adverse events will be defined as events resulting in one of the following outcomes: a) death; b) life-threatening situation; c) persistent or significant disability/incapacity; d) prolonged hospitalization; e) any suspected transmission of an infectious agent via a medicinal product; f) any clinically significant event.

Serious adverse events will be reported to the Research Ethics Committee (REC), in accordance with the guidelines of *Comissão Nacional de Ética em Pesquisa/Secretaria-Executiva do Conselho Nacional de Saúde/Ministério da Saúde* (CONEP/SECNS/MS) Circular Letter No. 13/2020. In the event of a reaction to the drug or an adverse event that the site investigator considers related to methylene blue, administration of the drug must be discontinued.

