### Outcomes

The primary outcome will be a composite consisting of any of the following events: (1) initiation of vasopressor therapy or an increase in vasopressor dose by at least 20% from baseline; (2) interruption of the RRT session; (3) interruption of fluid removal at the request of the attending physician at any point during the session. No predefined interruption criteria were established due to the wide range of clinical scenarios encountered in patients undergoing RRT; thus, decisions regarding treatment interruption were left entirely to the attending physician's discretion and will not be adjudicated.

Secondary outcomes include the occurrence of hypotension during the RRT session, the maximum vasopressor dose within the first 24 hours after the hemodialysis session, the cumulative norepinephrine equivalent (NEE) dose,^(15)^ the RRT session fluid balance, the 24-hour fluid balance, ICU mortality, and in-hospital mortality. Hypotension will be defined as a sustained drop in mean arterial pressure (MAP) below 65mmHg. We will assess potential adverse events related to methylene blue use, specifically: acute myocardial infarction, hemolytic anemia, cardiopulmonary arrest during the session, and worsening of gas exchange. We will present all outcome data as specified in table 1S (Supplementary Material). The trial sequence is available in figure 2.

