### Data collection

Demographic characteristics, comorbidities, and severity of illness will be collected at baseline for all participants (Table 2S - Supplementary Material). Renal replacement therapy main characteristics and baseline hemodynamic data will be collected (Table 3S - Supplementary Material), and vital signs will be recorded every 15 minutes by the nursing team via invasive blood pressure or automated non-invasive blood pressure for the duration of the session, along with any changes in vasoactive drug use (Table 4S - Supplementary Material). We will collect variables assessed up to 24 hours, then participants will be followed until hospital discharge to determine survival status or death.

Participants who are withdrawn from the study for safety reasons (excluding those who withdraw consent) will be included in the analysis on an intention-to-treat basis. Any adverse events occurring within the first 24 hours after the hemodialysis session will be documented (Table 5S - Supplementary Material). Adherence to the intervention will also be recorded (Table 6S - Supplementary Material). The data collection schedule is presented in table 7S (Supplementary Material).

Data will be collected via electronic forms using the RedCap platform and securely stored. Forms will be completed by the investigators, who will use specific passwords to access them. Training will be provided for all personnel involved in the study to ensure high-quality data collection. The principal investigator will be available for any questions regarding form completion. Data consistency will be periodically reviewed, and any discrepancies will be addressed by contacting the sites for clarification and correction.

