#### Statistical analysis

Our primary analysis will follow a modified intention-to-treat (mITT) approach, including all randomized participants who consent to participate. As clinical management might change after randomization, we expect that some participants randomized will not undergo RRT, either because of clinical improvement or deterioration. Thus, mITT analysis will include only those participants who received RRT. The data analysis will be performed after the submission of the protocol paper and analysis plan for publication.

Categorical variables will be expressed as counts and percentages. Continuous variables will be presented as means and standard deviations (SD) or medians with interquartile ranges (IQR, 25^th^ - 75th percentile), as appropriate. For all outcomes, including the primary outcome, we will not impute missing data, and the number of missing values will be clearly presented in tables. Treatment adherence will be reported as receiving the medication as a bolus, as a continuous infusion, or both.

The composite primary outcome will be measured using a mixed logistic model adjusted for non-linear terms of age, baseline MAP, vasopressor dose, and study site. Vasopressor dose will be defined as noradrenaline dose equivalents.^(15)^ A per-protocol analysis will be performed, including only participants who received the assigned medication. Additionally, we will conduct a sensitivity analysis that considers only participants who received the medication as a bolus plus continuous infusion. In all primary outcome analyses, the estimand will be the marginal risk difference between the intervention and control groups, along with their 95% confidence intervals, using the R package. Odds ratios will also be reported. Age and MAP will be included as restricted cubic splines in the model. In case any model does not converge, a stepwise approach will be used: (1) remove cubic splines; (2) remove the random effect for the site; (3) use Poisson or binomial regression.

Secondary outcomes will be assessed using similar models for categorical outcomes and using linear models for continuous variables, with adjustment for age, baseline MAP, vasopressor dose. For secondary binary and exploratory outcomes, logistic regression will be used, with the effect estimate expressed as marginal differences. The frequency of adverse events will be expressed as counts and percentages, and comparisons.

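### General adverse events are counted only if linked to a drug that one arm never receives, and the special-interest window has no start in usual care, so safety ascertainment differs by arm

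*Protocol article*

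**What the plan says.** All references are to the protocol article.

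- **General definition (Safety and adverse events).** After noting that complications are anticipated in this population, the text says: "These events will only be considered adverse events if they are potentially related to the study treatment, are unexpected to the attending physician". A third condition is that they are unrelated to the illness that led to dialysis. The section repeats the filter: "expected abnormalities will not be considered adverse events unless there is suspicion or confirmation that the event is related to the study intervention".
- **Special-interest events (same section).** "Adverse events of special interest - those already known to be associated with methylene blue, regardless of severity - will also be recorded". The list includes hypertension, chest pain, hemolytic anemia and worsening gas exchange. The paragraph then asks for any event thought possibly drug-related and ends: "These data will be collected only within the first 24 hours following the drug infusion".
- **Data collection.** "Any adverse events occurring within the first 24 hours after the hemodialysis session will be documented".
- **Outcomes.** Four safety events are named: "acute myocardial infarction, hemolytic anemia, cardiopulmonary arrest during the session, and worsening of gas exchange".
- **Serious adverse events (Safety and adverse events).** These are defined by outcome (death, life-threatening situation and so on) and are adjudicated by independent physicians.
- **Use of the data.** Statistical analysis says: "The frequency of adverse events will be expressed as counts and percentages, and comparisons". The secondary objectives in the Introduction include adverse events among the effects of methylene blue to be evaluated. Under Sample size calculation and interim analysis, the DSMB reviews adverse event data.
- **Arms and blinding.** Under Interventions, usual care receives no methylene blue. Under Blinding, healthcare professionals cannot be blinded.

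**The concern.** A randomized safety comparison is informative only if an event has the same chance of being recorded in either arm. A definition that requires a possible link to the study drug breaks this when one arm gets no drug and no placebo. A control patient with the same clinical event has nothing to which it could be attributed. In the methylene blue arm, the link is considered at the bedside with the allocation known.

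The resulting error can go in either direction. Events that would have occurred anyway may be counted only on methylene blue, which looks like harm. A real excess may instead be put down to critical illness and leave the table. Either error would reach the final safety report and the DSMB's review. Control events that were never recorded cannot be recovered at analysis.

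**Working it through.** **1. Which events the filter reaches**

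| Stream | Relatedness condition per patient? | Consequence |
|---|---|---|
| General events, not serious and not listed | Yes, stated twice | Ascertainment differs by arm |
| Special-interest events | None stated; chosen by type, several with objective thresholds | Comparable if collected alike, but see step 2 |
| Serious adverse events | None in the outcome-based definition; independently adjudicated | Comparable if collected alike |
| Four events under Outcomes | None explicit, though introduced as potentially related to methylene blue | Comparable if collected alike, but see step 3 |

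**2. The two windows**

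Under Interventions, the bolus is given over 5 minutes immediately before the session, the infusion runs throughout it, and a session lasts 2 to 6 hours. Ignoring the bolus:

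- Data collection: the window closes 24 h after the session ends, which is 26 to 30 h after it starts.
- Safety section, counted from the start of the infusion: the window closes 24 h after the session starts, which is 24 − 6 = 18 h to 24 − 2 = 22 h after it ends. The gap between the two windows is 2 to 6 h.
- Safety section, counted from the end of the infusion: the two windows nearly coincide in the methylene blue arm.
- In usual care, the safety-section window has no start under either reading. The sentence closes the paragraph that contains the special-interest list, so it governs that list.

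**3. The two lists**

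Hemolytic anemia and worsening gas exchange appear both under Outcomes and in the special-interest list. Acute myocardial infarction and cardiopulmonary arrest appear only under Outcomes. No sentence says whether the general filter applies to them.

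**4. Size of the distortion for filtered events**

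The article gives no adverse-event rate and names no test, so this is an illustration.

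Inputs:
- n = 130 per arm and a two-sided 0.05 level, both from the article.
- Assumed: the same true rate r in both arms (no real harm); a share q of methylene blue events judged related; none judged related in usual care; Fisher's exact test.
- The number analyzed may be below 130, because only participants who receive dialysis are included.

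Fisher two-sided p with 0 of 130 in usual care:
- 5 vs 0: p = 0.060
- 6 vs 0: p = 0.029
- 7 vs 0: p = 0.014

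Six recorded events are therefore enough for nominal significance. With X ~ Binomial(130, r·q), the chance of a false harm signal is P(X ≥ 6):

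| True rate r | q = 0.25 | q = 0.5 | q = 1 |
|---|---|---|---|
| 5% | 0.6% | 11% | 64% |
| 10% | 11% | 64% | 99% |
| 20% | 64% | 99% | >99.9% |

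For example, with r = 10% and q = 0.5, the expected recorded count on methylene blue is 130 × 0.10 × 0.5 = 6.5, against 0 in usual care, although the true expectation is 13 in each arm.

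In the opposite direction, as q approaches 0 the methylene blue count also approaches 0, whatever the true excess.

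**The case against.** The strongest reply is that most of the important safety data escape the filter. Special-interest events are selected by type, and gastric reflux is even timed from the start of dialysis, which both arms have. Serious adverse events are defined by outcome and adjudicated independently. Cardiac arrest, and commonly infarction, would qualify as serious, and the special-interest list is introduced as a set of inclusions that need not be exhaustive. Data collection already supplies a window that works in both arms. The article does not say who judges relatedness under the general definition, and it says outcome assessors are blinded. The planned comparison is an unfinished phrase with no event set or test. The supplementary adverse-event table and the notes that the article cites are not at hand, so the forms may already be symmetric.

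Much of this stands. A reader might infer that usual-care patients cannot have any adverse event and that every safety comparison is invalid. The documents do not support that: three streams carry no explicit patient-level relatedness condition. A reader might also infer that infarction and arrest are certainly filtered out, but the text only leaves their handling unclear. That the comparison is between arms is itself inferred, from the secondary objectives and the statistical section, though it is the natural reading.

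The reply does not remove the stated rule for general events. It also does not supply a control-arm start for the window that follows the special-interest list, or resolve the conflict between the two windows.

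**Conclusion.** The concern holds for general adverse events, meaning those that are neither serious nor named. Their definition makes ascertainment depend on the arm, so a between-arm comparison of them is biased. Under the assumptions shown, the chance of a false harm signal for these events ranges from 0.6% to nearly 100%. The range is wide because the documents give neither an event rate nor the share likely to be judged related, and it presumes that no control event is judged related. It says nothing about unfiltered events.

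Separately, the safety window in Safety and adverse events has no start in usual care and conflicts with Data collection. Acute myocardial infarction and cardiopulmonary arrest also need consistent handling between Outcomes and the safety section.

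The primary outcome, its sample size and the interim p < 0.01 harm rule, which the article ties to the primary outcome, are not affected. The DSMB's review of adverse event data is affected.

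**What to change.** 1. Record the four events named under Outcomes, the special-interest events and all serious adverse events in both arms, regardless of relatedness or expectedness.
2. Add acute myocardial infarction and cardiopulmonary arrest to the special-interest list, so that it agrees with Outcomes.
3. Reconcile Data collection with Safety and adverse events by using one window anchored on the dialysis session, for example from its start to 24 h after its end. Starting at the beginning of the session also covers arrest during the session, which Outcomes names.
4. State that these counts are the ones compared between arms. Keep relatedness as a separate field used for reporting, and do not use it to decide whether an event is recorded.

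The cost is revised protocol and form wording and some additional entries for control patients. No new procedure is needed. The change should be made while data are still being collected, because missing control events cannot be restored later.

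### The adverse-event definition gives two opposite answers for an expected event suspected to be related to methylene blue

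*Protocol article*

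**What the plan says.** All the relevant rules but one stand in the Protocol article, *Safety and adverse events*.

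- **First paragraph.** After saying that complications are anticipated in this population, it sets a gate: "These events will only be considered adverse events if they are potentially related to the study treatment", and further that they "are unexpected to the attending physician, and are unrelated to the underlying critical illness that led to RRT".
- **Third paragraph.** It notes that "various physiological alterations are expected, including laboratory abnormalities and vital sign changes, as well as those resulting from ongoing treatments", and concludes that "expected abnormalities will not be considered adverse events unless there is suspicion or confirmation that the event is related to the study intervention".
- **Fourth paragraph.** Events of special interest, described as "those already known to be associated with methylene blue, regardless of severity - will also be recorded", are collected separately. The paragraph also holds a catch-all: "any adverse events deemed by investigators to be possibly related to the study drug must also be documented".

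No sentence ranks the first paragraph against the third. The remaining rule is in *Statistical analysis*, which says how the result is used: "The frequency of adverse events will be expressed as counts and percentages, and comparisons". Under *Sample size calculation and interim analysis*, the data and safety monitoring board (DSMB) also reviews adverse-event data at the interim look after 100 participants.

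**The concern.** The first paragraph joins three conditions with an *and* under an *only if*, so each is necessary. Being expected is then enough to disqualify an event, however strongly the investigator suspects the drug. The third paragraph makes suspicion of the drug the one thing that rescues an expected event. A site cannot follow both.

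The first paragraph is also strained within itself. It introduces complications that the trial team anticipates and then requires them to be unexpected.

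What is at stake is the completeness and consistency of the adverse-event count. A site that follows the first paragraph would leave out suspected drug-related events that a site following the third would record. An event that was never recorded cannot be recovered at analysis. The count feeds the final table and the DSMB's review. The primary efficacy analysis is not affected.

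**Working it through.** The documents give no adverse-event rate, so no arithmetic applies. The check is to put every kind of event through both rules.

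Three yes/no attributes matter: R, a relation to the intervention is suspected; E, the event was expected; I, the event is linked to the underlying critical illness.

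- First paragraph: adverse event only if R and not E and not I.
- Third paragraph: applies only when E is yes, and then adverse event if R.

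| R | E | I | First paragraph | Third paragraph | Result |
|---|---|---|---|---|---|
| yes | yes | no | not counted | counted | conflict |
| yes | yes | yes | not counted | counted | conflict |
| no | yes | no | not counted | not counted | agree |
| no | yes | yes | not counted | not counted | agree |
| yes | no | no | can count | silent | no conflict |
| yes | no | yes | not counted | silent | no conflict |
| no | no | no | not counted | silent | no conflict |
| no | no | yes | not counted | silent | no conflict |

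Two of the eight cells conflict, two agree, and in four the third paragraph does not speak. The conflicting cells are exactly those in which the event was both expected and suspected to be related. A contribution from the illness does not widen this set. Where the event was unexpected but the illness played a part, the first paragraph excludes it and the third says nothing, so the only tension there is with the catch-all.

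Next, whether other text settles the two conflicting cells:

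- **Catch-all, fourth paragraph.** It asks only for a possible relation and sets no expectedness condition, so it leans towards the third paragraph. But it speaks of adverse events, and what qualifies as one is the point in dispute.
- **Events of special interest.** Reactions already known for methylene blue are recorded under either rule. This removes them from the affected set.
- ***Outcomes*.** Acute myocardial infarction, hemolytic anemia, cardiopulmonary arrest during the session and worsening of gas exchange are prespecified for assessment. This removes them too.

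What remains exposed is an expected event, suspected to be related to the intervention, that is neither a known methylene blue reaction nor prespecified under *Outcomes*.

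**The case against.** Several points on the other side are sound and limit the finding.

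- **Different scopes.** The first paragraph speaks of complications, the third of physiological, laboratory and vital-sign changes, so the two might be meant for different things. The text draws no such boundary, and the categories overlap: a change in blood pressure can be both. This does not remove the conflict.
- **Known drug reactions.** A reader might infer that a recognised methylene blue reaction drops out because it is recognised. The documents do not support that. Special-interest events are defined by being known for the drug, and the named events are introduced as inclusions, so the list need not be closed. Read in context, *unexpected* most naturally refers to the clinical course of a severely ill dialysis patient, not to the drug's profile. This objection stands.
- **Deaths and arrests.** A reader might infer that an expected death or arrest suspected to be drug-related would never reach the DSMB. The article defines serious adverse events by their outcome and does not say that they must first pass the first paragraph's gate. In-session arrest is prespecified, and ICU and in-hospital mortality are secondary outcomes for all participants. This objection stands.
- **Interim rule.** The one numerical stopping rule, p < 0.01 for harm, is tied to the primary outcome and not to adverse-event counts. That is right, though the DSMB reviews adverse events as well.
- **Unseen material.** The article refers to notes and to Table 5S for adverse-event detail, and the form may already hold fields for relatedness and expectedness. That bears on the cost of the fix and on how much sites would differ in practice. It does not excuse the conflict, because the article states two rules that disagree; it does not merely leave one out.

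**Conclusion.** The contradiction is real and stands in the current text. For an expected event with a suspected or confirmed relation to the intervention, the first paragraph says it is not an adverse event and the third says it is, with no order of precedence.

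Its reach is limited to such events outside the special-interest class and outside the list under *Outcomes*. Illness contribution adds a direct conflict with the third paragraph only when the event was also expected.

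The size cannot be stated. It would need both the rate of suspected-related events and the share of them that were expected, and the article gives neither. Any percentage would only restate an assumed share. The direction is clear: following the first paragraph records fewer suspected drug-related events than following the third. That sites would in fact differ is a possibility the text leaves open, not something it shows.

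The conclusion assumes that *only if* and *and* in the first paragraph carry their ordinary meaning. It says nothing about whether relatedness can be judged alike in the two arms of an open-label trial, which is a separate matter. The change is worth making because the stated exclusion rule loses suspected drug-related events and the correction is cheap.

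**What to change.** Reconcile the first and third paragraphs of *Safety and adverse events* into one definition. Remove unexpectedness and absence of a link to the critical illness as conditions for counting, and keep the rule that the third paragraph already states. For example: *an event is an adverse event when its relation to the study intervention is suspected or confirmed, whether or not it was expected and whether or not the critical illness may also have contributed.* This agrees with the catch-all in the fourth paragraph and gives that sentence a settled meaning. The special-interest events and those prespecified under *Outcomes* stay as they are.

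Record expectedness and alternative cause as fields on the adverse-event form, if it does not already hold them, and use them to classify events, not to decide whether they count.

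The cost is about one sentence of protocol text, a note in site training and at most two form fields. The downside is that sites will record somewhat more events.

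### Hemolytic anemia is a named safety outcome with a three-part definition but is collected for 24 hours only, so later cases may be missed and a low count supports only a 24-hour statement

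*Protocol article*

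**What the plan says.** The Outcomes section of the protocol article lists the adverse events to be assessed: "acute myocardial infarction, hemolytic anemia, cardiopulmonary arrest during the session, and worsening of gas exchange". The Safety and adverse events section includes hemolytic anemia among the events of special interest, which it describes as already linked to the drug and to be recorded whatever their severity. Its definition is "hemolytic anemia (defined by the presence of anemia accompanied by clinical signs such as jaundice, together with laboratory evidence of red blood cell destruction", the last element being illustrated by "such as elevated lactate dehydrogenase - LDH, increased indirect bilirubin, low haptoglobin, and/or reticulocytosis".

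The paragraph with these definitions also asks for any event that investigators think may be related to the drug, and closes with the time limit: "These data will be collected only within the first 24 hours following the drug infusion".

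The Data collection section gives the same length with a different starting point: "Any adverse events occurring within the first 24 hours after the hemodialysis session will be documented". Of the period after the 24-hour variables it says only: "then participants will be followed until hospital discharge to determine survival status or death".

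**The concern.** The definition joins three elements, so a case becomes countable only when the last of them is present. Collection stops at 24 hours for every event of special interest, whether it is an immediate reaction such as vomiting or a condition that has to be built up from clinical and laboratory findings. The article gives no reason why 24 hours suits hemolytic anemia. It does set an event-specific period elsewhere in the same paragraph: gastric reflux is judged over 6 hours from the start of dialysis.

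Adverse events are among the secondary objectives in the Introduction. If some cases complete the definition after the window closes, the reported count will be too low, and a reader who sees few or no cases may take that as evidence about the drug when it is partly a product of the window.

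**Working it through.** **1. What happens to a case that completes the definition after 24 hours**

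- Special-interest route: closed, because the limit is worded as exclusive.
- Investigator-suspected event: named in the same paragraph, so the same limit applies.
- Ordinary adverse event: the Data collection section also stops at 24 hours. In addition, the Safety section requires such events to be unexpected by the treating physician, which is doubtful for an effect the article treats as known. It sets expected laboratory abnormalities aside unless a link to the intervention is suspected or confirmed.
- Serious adverse event: the definition carries no time limit of its own, so a late serious case might be reported this way. A late non-serious case would not.
- Follow-up to discharge: described for vital status only.

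So the article describes no route that reliably counts a late case.

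**2. What the definition does not say**

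It sets no minimum time. Jaundice is an example of a clinical sign. The laboratory list is open and joined by and/or, so lactate dehydrogenase, indirect bilirubin or haptoglobin can satisfy it without reticulocytosis. A case can therefore qualify inside 24 hours. The share that does so, f, appears nowhere in the documents and is treated below as an assumption.

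**3. The plan's own figure**

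The article gives no number for this point. The group size used below comes from its sample size section (90% versus 75%, two-sided alpha 0.05, power 90%). With unpooled variances:

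n = (1.960 + 1.282)² × (0.90 × 0.10 + 0.75 × 0.25) / 0.15² = 10.51 × 0.2775 / 0.0225 = 129.6, rounded up to 130 per group.

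The stated 130 is reproduced. A longer safety window does not change it.

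**4. What a zero count would mean**

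Let p be the true risk in treated participants. The probability of a recorded case is p × f. After 0 of 130, the one-sided 95% upper bound on p × f is

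1 − 0.05^(1/130) = 0.0228, or 2.3%.

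The bound on p is therefore 2.3%/f. For comparison, the chance of recording no case when p is assumed to be 2% is (1 − 0.02 × f)^130.

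| Assumed f | Upper bound on p after 0/130 | Chance of zero recorded if p = 2% |
|---|---|---|
| 1 | 2.3% | 7% |
| 0.75 | 3.0% | 14% |
| 0.5 | 4.6% | 27% |
| 0.25 | 9.1% | 52% |
| 0.1 | 22.8% | 77% |

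Both p and f are illustrative. At f = 1 the window costs nothing, and the loss grows as f falls.

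**5. When the 24 hours start**

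One section counts from the drug infusion, the other from the dialysis session. Under Interventions, the bolus is given just before the session and the infusion runs throughout it, and sessions last 2 to 6 hours. If the first clock starts when the infusion begins and the second when the session ends, they differ by about 2 to 6 hours. The usual care arm receives no infusion, so the first clock has no start there.

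**The case against.** The strongest objection is that nothing in the documents shows 24 hours to be too short. They give no time to onset for hemolysis or for any marker, and the definition can be met early. This stands. A reader might infer that the trial cannot observe hemolytic anemia at all. That would require f to be exactly 0, which the documents do not support. They support only that later cases may be missed.

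A reader might also infer that serious events involving prolonged hospitalization or lasting disability cannot be established under a 24-hour rule. The Data collection rule concerns when an event occurs. An event that begins inside the window can be classified as serious later, so that inference fails.

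The Discussion's remark that the drug has few side effects might be read as an advance safety claim. It is background. For adverse events the Statistical analysis section promises only counts, percentages and comparisons, and the Discussion already lists the lack of long-term follow-up as a limitation.

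Finally, the supplementary tables on adverse events and on the collection schedule are not at hand, so which hemolysis markers are scheduled cannot be judged. This limits what can be said about detection inside the window. It does not remove the limit, because a schedule that ran longer would contradict the exclusive wording of the main text.

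**Conclusion.** The point holds as a stated collection rule that can under-count a named safety outcome. A low or zero count of hemolytic anemia would support a statement about the first 24 hours only. The size of the under-count cannot be derived from the documents: after 0/130 the upper bound is 2.3% with full capture and 2.3%/f otherwise, or 4.6% if half of the cases are captured.

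These figures assume 130 treated participants with safety data and a constant f. The modified intention-to-treat set leaves out participants who do not undergo dialysis, so the denominator may be somewhat smaller and the bounds slightly wider. The primary outcome and its analysis are unaffected. This is a worthwhile, low-cost improvement to the safety data.

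**What to change.** - Keep 24 hours for the acute events.
- For hemolytic anemia, extend collection beyond 24 hours in both arms, for example to day 7 or hospital discharge if earlier, using routine chart and laboratory results.
- Count from the start of the index session, so that both arms have the same defined start.
- Reconcile the Data collection and Safety and adverse events sections on when the 24 hours begin.
- If the window is not extended, state in the analysis and the report that the hemolysis result covers the first 24 hours only.

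The cost is a protocol amendment and one extra form for participants who are already followed to discharge. That follow-up is at present described for survival only, so the form is new collection. Some late hemolysis from other causes will be recorded, but in both arms, where the comparison can take account of it. Completeness will depend on which markers are measured in routine care, so reporting how many participants in each arm had them measured would help the reader interpret the count.
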